### Muscle biopsy

Participants are instructed to fast for 9 h prior to the biopsy visit. TLFB, blood pressure, weight, and waist and hip circumference are collected. Following the 0 h blood collection, participants consume a defined (calorie and nutrient composition) meal (i.e., Ensure, Carnation Instant Breakfast). Ninety (90) minutes later, a skeletal muscle biopsy is performed under ultrasound guidance by interventional radiologists associated with LSUHSC-NO. Using sterile technique, 2 cc of 2% lidocaine is injected at the incision site on the right vastus lateralis muscle. A 14-gauge core needle is inserted through a single-entry point. Samples of the vastus lateralis are obtained on 6 passes. Pressure is held on the biopsy site for 5 min, followed by pressure dressing for 1 h. After that time, the dressing is removed. Participants are contacted 24 h later to inquire about any adverse events and reminded to contact study personnel if any adverse events were to occur. Muscle biopsies are performed at two timepoints, the first one at least a week before the first exercise session and the second 5 days after the last exercise session.

### Fitness assessment

Approximately 5–7 days following the pre-intervention muscle biopsy, cardiorespiratory fitness (CRF) is assessed on a treadmill at the LSUHSC-NO Wellness Center using a modified Balke protocol. Following a brief warm-up period, participants begin the assessment by walking at brisk pace and level grade for 2 min, after which grade is increased 2% every 2 min until the computer software recommends stopping the assessment or volitional exhaustion is achieved. Estimated maximal oxygen uptake (VO_2max_) is calculated from the exercise test. In addition to VO_2max_, estimated metabolic equivalents (METs) are calculated from the speed and maximal grade achieved during the exercise test using standard equations from the American College of Sports Medicine’s Guidelines for Exercise Testing and Prescription (ACSM’s Guidelines for Exercise Testing and Prescription, 9th ed. 2014). Heart rate is monitored throughout the test to ensure safety and for accurate prescription of the exercise intervention. After the conclusion of the test, the participant goes through a cool down period. A wall push-up test is also performed to assess upper body muscular endurance. A personalized treadmill exercise prescription is developed based on the RHR recorded during the ECG. The heart rate responses to the graded exercise test for each participant is determined to achieve a level of moderate intensity (40–60% HRR) during the exercise program. Target heart rate (THR) ranges are calculated using the following equation: THR = %HRR * (HR_max_—RHR) + RHR, where %HRR is the percentage of HRR that defines the lower and upper ends of the target range (i.e., 0.40, 0.50, or 0.60). HR_max_ is the age-predicted maximum heart rate (220—age [yrs]). Using this data, an initial speed and incline for treadmill exercise is prescribed for each participant and adjusted as needed to achieve the desired exercise intensity for each exercise session. While speed and incline both increase throughout the intervention period, participant preferences dictate which variable increases first and more frequently. The participants are also provided with an accelerometer (i.e., Fitbit Zip) to monitor daily activity and steps. The fitness assessments are performed at two timepoints and constitute the first exercise session and the last exercise session.

### Exercise intervention

The moderate intensity aerobic exercise protocol is implemented 3 days per week for 10 weeks at the LSUHSC-NO Wellness Center. Each exercise session lasts for 30–42 min on a treadmill. The first and last 6 min are dedicated to warm-up and cool-down, respectively. The exercise begins at the lower end of the moderate intensity range (40–50% of HRR) for the first 4 weeks with progressive increases in duration. Beginning week 5, participants progress to the higher end of the moderate intensity range (50–60% of HRR). The duration of exercise sessions remains constant after week 4 so the absolute dose of exercise is altered through increasing intensity, i.e., from low-moderate to more vigorous, by increasing grade and/or speed. The speed, grade, heart rate and rating of perceived exertion (RPE) is monitored every three minutes during every session. The 24 h food recall questionnaire (ASA24), quality of life questionnaire (SF-36), Hospital depression and anxiety questionnaire, and Montreal Cognitive Assessment Test (MoCA) are administered before and after the 10-week exercise intervention period. The exercise sessions are one-on-one, and the participants appreciate the social interactions with the personnel who perform the sessions. Participants are contacted via their preferred method of communication (text or phone call) to remind them of each appointment. They are contacted if they do not come for the appointment to ascertain the reason and reschedule the visit. Participants are required to complete at least 80% of the sessions within the 10-week exercise intervention period. Participants are allowed to reschedule sessions within the same week. However, if participants miss 6 consecutive exercise sessions without rescheduling, they are removed from the study. Study personnel also send motivational texts to the participants. The incentive for exercise sessions was increased to account for the increased costs associated with transportation and to cover additional incidental expenses.

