**Methods:**

The Alcohol & Metabolic Comorbidities in PLWH: Evidence Driven Interventions Study (ALIVE-Ex Study, NCT03299205) is a longitudinal, prospective, interventional study to determine the effects of an aerobic exercise protocol on improving dysglycemia among PLWH with at-risk alcohol use. The intervention is a moderate intensity aerobic exercise protocol implemented 3 days per week for 10 weeks at the Louisiana State University Health Sciences Center-New Orleans. Participants who have a fasting blood glucose level between 94 and 125 mg/dl will be enrolled in the study. Oral glucose tolerance tests, fitness assessments, and skeletal muscle biopsies will be performed pre- and post-exercise intervention. The primary outcome is to determine whether the exercise protocol improves measures of whole-body glucose-insulin dynamics, cardiorespiratory fitness, and skeletal muscle metabolic and bioenergetic function. Secondary outcomes are to determine whether the exercise intervention improves cognitive function and overall quality of life. Results generated will demonstrate the effect of exercise on glycemic measures in PLWH with subclinical dysglycemia and at-risk alcohol use.

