Evidence suggests that people engaging in regular aerobic exercise preserve or improve glycemic control, cardiovascular function, skeletal muscle function, have reduced risk of metabolic syndrome, and improved quality of life [22, 23]. Specifically, structured walking for approximately 30 min three times per week reduces fasting glucose, hemoglobin A1c, and HOMA-IR [24, 25]. Moreover, PLWH engaging in exercise have increased energy, improved self-concept, increased physical fitness, mental health, improved cardiometabolic measures, body composition and immune function [23, 26–30]. Studies show that moderate intensity exercise (40–60% heart rate reserve [HRR]) improves mitochondrial dysfunction, insulin resistance and diabetes among PLWH [31]. Additionally, our studies in the preclinical SIV model provided evidence that ex vivo β2 adrenergic stimulation of muscle myoblasts improved mitochondrial bioenergetics and mitochondrial copy number [21] supporting the hypothesis that aerobic exercise may improve mitochondrial homeostatic mechanisms resulting in improved glycemic control. Despite compelling evidence that exercise can be an effective strategy to improve metabolic health, little is known of how exercise improves metabolic health in PLWH, particularly those with at-risk alcohol use.

Based on our preclinical and clinical observational studies and evidence from the literature, we launched the Alcohol & Metabolic Comorbidities in PLWH: Evidence Driven Interventions Study (ALIVE-Ex Study, NCT03299205). This is an ongoing longitudinal prospective, interventional study investigating the effects of aerobic exercise in PLWH with fasting dysglycemia and at-risk alcohol use. The study consists of two phases. The objective of the first phase was to determine whether PLWH with at-risk alcohol use had increased risk of dysglycemia and dysregulated muscle metabolic function. The overall objective of the second phase of the study is to determine whether moderate intensity aerobic exercise will improve measures of whole-body glucose insulin dynamics and improve skeletal muscle metabolic and bioenergetic function. The secondary objective of Phase 2 is to determine whether the exercise intervention improves cognitive function and overall quality of life.

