#### Secondary outcomes

Changes in alcohol use are assessed using TLFB and Peth pre- and post-exercise intervention. Healthy Eating index (HEI) using Automated Self-Administered 24-h Dietary Assessment Tool (ASA24); Montreal Cognitive Assessment (MoCA); Hospital Anxiety and Depression Scale (HADS); and 36-Item Short Form Health Survey (SF-36) scores; pre and post exercise intervention are used to assess changes in dietary patterns, cognitive ability, and overall quality of life. The ASA24 is based upon the United States Department of Agriculture's (USDA) Automated Multiple-Pass Method (AMPM). Data from multiple validation and evaluation studies indicate good to strong agreement between the ASA24 system and standardized interviewer-administered 24-h recalls. Furthermore, data are well estimated for HEI scores based on the 24-h dietary recall [35]. The reliability of MoCA is 0.89, and the intraclass correlation coefficient of 0.955 and is shown to be good. Additionally, with a cut-off of 26 points, a sensitivity of 80% and specificity of 75% is reported [36]. The HADS has been found to perform well in assessing the symptom severity and presence of anxiety disorders and depression symptoms in both somatic, psychiatric, and primary care patients and in the general population [37]. Finally, the SF-36 was developed as a set of generic, coherent, and easily administered quality-of-life (QOL) measures. These measures rely upon participant self-reporting, provide a direct quantitative indication of an individual's health status, and is widely used as a QOL evaluation tool [38, 39].

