### Data management and analysis

All data are entered into REDCap and are handled with confidentiality. Personal information of participants such as phone number and email addresses are used only to contact the participant. Names of participants appear only in the demographic form. The participants’ demographic and outcome measures of interest pre- and post-exercise intervention will be summarized using descriptive statistics. Mean, standard deviation, and range will be calculated for continuous variables, and frequencies and percentages will be generated for categorical variables. For continuous variables (such as VO_2max_, OCR, ECAR), the normal distribution assumptions will be tested. If necessary, the data will be transformed to follow the normal distribution assumption. If the normality assumption cannot be met, these variables will be classified as categorical or analyzed using non-parametric tests. For categorical variables (e.g., glucose at 2 h, HOMA-IR, HOMA-b) clinical cutoff values will also be used. The changes in the outcome measures (e.g., OGTT outcomes, bioenergetic measures, microRNA expression, RHR, VO_2max_, MOCA measures, ASA24 measures) between pre and post exercise intervention will be tested using the paired t-test. Linear regression models will also be used to analyze the relationship between alcohol use with the outcome measure changes as the dependent variable, adjusting for potential confounding factors (such as age, sex, race, viral load and CD4 counts). If there is matching or balance achieved, age and gender will be used as categorical variables rather than confounders. A p < 0.05 will be used for statistical significance.

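### A MoCA gain tested by paired t-test without an unexercised comparison cannot be credited to exercise, because any retest gain would count as benefit

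*Protocol article*

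**What the plan says.** All references are to the protocol article.

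- **Timing.** Under Exercise intervention, the questionnaires and "Montreal Cognitive Assessment Test (MoCA) are administered before and after the 10-week exercise intervention period".
- **Test.** Under Data management and analysis, the outcomes whose change is tested include "MOCA measures, ASA24 measures". Changes "between pre and post exercise intervention will be tested using the paired t-test", and "A p < 0.05 will be used for statistical significance". Sidedness is not stated.
- **Aim.** The Background says: "The secondary objective of Phase 2 is to determine whether the exercise intervention improves cognitive function and overall quality of life". The abstract repeats it: "Secondary outcomes are to determine whether the exercise intervention improves cognitive function and overall quality of life". The Results section adds that the analysis will show whether cognitive measures improve.
- **Design.** The abstract says the study "is a longitudinal, prospective, interventional study to determine the effects of an aerobic exercise protocol". No control, waiting-list or other non-exercising group is described.
- **Instrument.** Under Secondary outcomes, "The reliability of MoCA is 0.89", followed by an intraclass correlation of 0.955. Similar psychometric notes are given for the other instruments.
- **Other analyses of change.** Regression models relate outcome changes to alcohol use (Data management and analysis). A dose-response analysis is planned where exercise sessions are missed (Handling of missing data).

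**The concern.** The null hypothesis of the paired t-test is zero mean change. That is the right reference only if scores would stay level without exercise. Plasma glucose or oxygen consumption cannot be learned, but a short cognitive test can be, at least in principle. If familiarity lifts the second score, the test can reject although exercise did nothing, and it does so in the hoped-for direction.

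High reliability gives no protection. A gain shared by all participants leaves the correlation between sittings unchanged. High reliability also makes the SD of change smaller, so a small common gain reaches significance more easily.

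What is at stake is the cognitive part of the secondary objective. A reader told that MoCA rose with p < 0.05, in a study set up to determine whether exercise improves cognition, would take it as evidence that it does.

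**Working it through.** The article gives no sample size calculation, power or expected MoCA change, so there is no stated figure to reproduce. The check asks how often the planned test would be significant if exercise had no effect and only a retest gain were present.

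**Inputs from the article**
- n = 33, the number who had completed exercise and the post-intervention fitness, OGTT and biopsy assessments by November 2022 (Results). MoCA is not named in that count, so using it here is an approximation.
- Alpha 0.05, taken as two-sided.
- r = 0.89, the stated reliability, used as the correlation between the two sittings. The article does not say what kind of reliability this is.

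**Assumed inputs, not in the article**
- Retest gain g of 0.25, 0.5 or 1.0 point.
- Between-person MoCA SD of 3 or 4 points.
- A direct alternative for the SD of change of 2.5 points.

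**Step 1: SD of change**

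SD of change = SD × √(2(1 − r)) = SD × √0.22 = 0.469 × SD.
- SD 3: 0.469 × 3 = 1.41
- SD 4: 0.469 × 4 = 1.88

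**Step 2: smallest mean change that is significant**

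With 32 degrees of freedom the critical t is 2.037, and the threshold is 2.037 × SD of change / √33.
- SD of change 1.41: 0.50 point
- SD of change 1.88: 0.67 point
- SD of change 2.5: 0.89 point

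The test would therefore respond to mean shifts of half a point to just under one point, whatever their cause.

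**Step 3: probability of p < 0.05 with no exercise effect**

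The test statistic follows a noncentral t distribution with 32 degrees of freedom and noncentrality g × √33 / SD of change. For g = 0.5 and SD of change 1.41, this is 0.5 × 5.745 / 1.407 = 2.04, and the rejection probability is 51%.

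| SD of change | g = 0.25 | g = 0.5 | g = 1.0 |
|---|---|---|---|
| 1.41 | 17% | 51% | 98% |
| 1.88 | 12% | 32% | 84% |
| 2.5 | 9% | 20% | 61% |

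With g = 0 the figure is 5%, of which 2.5% is in the direction of improvement.

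**Step 4: sensitivity to the correlation**
- r = 0.955 (the stated intraclass correlation), SD 3: SD of change 0.90. A gain of 0.5 point gives 87%.
- r = 0.70 (assumed), SD 4: SD of change 3.10. Gains of 0.5 and 1.0 point give about 14% and 44% in the direction of improvement.

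**Step 5: the source of the inflation**

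In a simulation of 20,000 trials with SD 3 and r = 0.89, a non-exercising arm of equal size (33 per arm) was given the same retest gain. The between-arm test of change was significant in 4.9% of trials at g = 0.5 and 5.1% at g = 1.0. The inflation comes from the missing comparison, not from the t-test as such.

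**The case against.** The strongest reply is that the article contains no evidence of a MoCA retest gain at 10 weeks, neither that it exists nor how large it is. The percentages above follow the assumed gain and SD. This stands: they show what would happen if there were a gain, not what will happen.

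Several stronger readings are tempting, and the article does not support them.

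- **That the same MoCA form is used twice.** The article is silent on versions. That is operational detail usually left to the full protocol or procedures, so the silence shows nothing either way.
- **That reliability is offered as protection against learning.** The figures appear as routine description, alongside similar notes for the other instruments.
- **That the plan has no internal contrast at all.** A uniform retest gain should not vary with sessions attended, so the dose-response analysis is a partial check. It applies only where sessions are missed, and participants must complete at least 80% of sessions, so the range of exposure is narrow. A uniform gain also cancels from the regression on alcohol use, but that regression does not compare exercise with no exercise. Neither analysis supplies an unexercised retest.

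It can also be said that every pre-post outcome shares the single-arm design and that a paired t-test is the ordinary test for such data. Both are true. MoCA still merits separate mention because learning is a cause of change that the laboratory outcomes do not have. The section on limitations mentions neither retest effects nor the lack of a comparison group.

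**Conclusion.** The point holds as a limit on interpretation. The plan as written would let p < 0.05 on an uncontrolled, learnable performance test be read as a cognitive benefit of exercise, and no planned analysis separates the two.

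The size is conditional. For assumed gains of 0.25 to 1.0 point, 33 participants and an SD of change of 1.4 to 2.5 points, a significant result with no exercise effect would occur in about 9% to 98% of trials. So wide a range supports saying that a retest gain could be reported as benefit. A reader might infer that it will be, or that the false-positive rate is known to be far above 5%. The article gives no figure that would establish either.

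The consequence is minor for the study as a whole. MoCA is a secondary outcome, and retest learning does not touch the glucose, insulin or muscle measures.

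**What to change.** 1. **Data management and analysis, and the anticipated findings in Results.** Report MoCA change for all participants as a mean change with its 95% confidence interval, labelled descriptive. State that p < 0.05 on this outcome will not be taken as evidence that exercise improved cognition, because retest learning cannot be separated from an exercise effect. This costs a sentence or two, needs no new data, and covers participants already tested.
2. **Participants still to be tested, if any, and if not already done.** Use alternate MoCA versions at the two sittings, alternate their order across participants, and record the version. This costs a data field and a line in the procedures. It brings some version-to-version noise and mixes administration regimes between earlier and later participants. Familiarity with the type of task and other time effects would remain, so this step supplements the first and does not replace it.

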### Criteria for modifying exercise protocol

Inability of participants to use the treadmill, such as orthopedic limitations, is addressed by conducting the sessions using a stationary bike with moving arms, and the exercise intensity is matched to that of using the treadmill.

### Outcome measures

#### OGTT

Outcome measures are determined as previously described [32]. Briefly, plasma glucose is measured at 0, 1 and 2 h using a glucose Analox analyzer (GM7 Analox microstat, Analox Instruments, USA) and area under the curve calculated. Plasma insulin and C-peptide are measured at 0, 1 and 2 h using ELISAs (Millipore Human Insulin ELISA, cat.no. EZHI-14 K; Alpco C-Peptide ELISA, cat.no. 80-CPTHU-E10.1). HOMA-IR is calculated (fasting glucose (mg/dL) x fasting insulin (µU/mL) divided by 405) and HOMA-β is calculated as 60 × fasting insulin (μU/mL) / (fasting glucose (mg/dL)—63). High molecular weight adiponectin is measured in the baseline samples using an ELISA (Alpco HMW Adiponectin ELISA, cat.no. 80-ADPHU-E01).

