## Background

With effective antiretroviral therapy (ART), people living with HIV (PLWH) have near normal life expectancy and increased risk of age-associated comorbidities. Cardiometabolic comorbidities [1–6], are among the leading causes of morbidity and mortality among PLWH [1–5, 7, 8]. At-risk alcohol use is more frequent among PLWH than the general population and increases the risk of health challenges [9–11]. Our multidisciplinary research team is conducting a longitudinal clinical observational study, the New Orleans Alcohol and HIV study (NOAH) [12], to examine the impact of at-risk alcohol use on risk for comorbidities in PLWH. The study population is comprised of majority socioeconomically disadvantaged and majority Black/African American individuals in the Greater New Orleans Area. Data indicate that 57% have at-risk alcohol use [12], ~ 36% meet criteria for metabolic syndrome, ~ 50% have insulin resistance as measured by the Homeostatic Model Assessment of Insulin Resistance (HOMA-IR), and ~ 15% meet criteria for type 2 diabetes[13]. Results also showed a significant negative association between HOMA-β, a surrogate indicator of pancreatic cell function, and multiple measures of alcohol use including Alcohol Use Disorders Identification Test (AUDIT)-C, 30-d Timeline Followback (TLFB), and a biomarker of recent alcohol use Phosphatidylethanol (PEth) [13].

Previously, studies in simian immunodeficiency virus (SIV)-infected macaques, a preclinical model of HIV, showed that chronic binge alcohol (CBA) significantly impaired endocrine pancreatic response to a glucose load [14], and increased pathophysiological alterations in multiple metabolically active organs [15]. CBA administration also increased skeletal muscle proteasomal activity, impaired anabolic pathways and insulin signaling [16–19] and altered mitochondrial bioenergetic function [20, 21]. Together, these findings suggest that at-risk alcohol use increases risk of metabolic dysregulation in PLWH, and in a preclinical model of HIV infection, highlighting the importance of developing interventions to ameliorate disease burden. Specifically, strategies to reduce cardiometabolic comorbidities and improve overall quality of life that can be scalable and can be implemented in clinical and community settings are urgently required to mitigate health disparities.

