**Fig. 1 Fig1:**
[figure not shown]
Study timeline for the Alive-Ex research protocol

**Table 1 Tab1:** Inclusion and exclusion criteria for the ALIVE-Ex Study

Inclusion criteria	Exclusion criteria
PLWH ≥ 18 years of age	Diagnosed diabetes (self-reported)
Fasting plasma glucose between 94 and 124 mg/dl	Lack of informed consent
Answered “No” to all questions of PAR-Q, with the exception that if participants answered “yes” to taking medications for high blood pressure, they were evaluated at medical clearance and enrolled into the study, based on the discretion of the cardiologist	Non-English speaking
	Females who are pregnant
	Acute alcohol intoxication on any visit days as determined by breathalyzer
	Additional exclusion criteria for exercise intervention
	Orthopedic or cardiovascular complications that preclude from exercise
	Peripheral neuropathies
	Allergy to lidocaine
	Use of anticoagulant medication (blood thinners)
	Acute illness within the preceding six weeks of study visit (fever, new antibiotic use, or unscheduled healthcare visit (for illness)

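### The printed HOMA-β formula has a multiplier of 60 where its own mg/dL constants call for 360; if the analysis follows the text, HOMA-β comes out at one-sixth of its proper size

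*Protocol article*

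**What the plan says.** The OGTT subsection under Outcome measures defines both indices in one sentence. For insulin resistance: "HOMA-IR is calculated (fasting glucose (mg/dL) x fasting insulin" (in µU/mL), with 405 as divisor. For β-cell function: "divided by 405) and HOMA-β is calculated as 60 × fasting insulin" (again in µU/mL), divided by "fasting glucose (mg/dL)—63", where the long dash is a minus sign. The units are explicit, and the article gives no other version of the formula.

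The Background section describes the index as "HOMA-β, a surrogate indicator of pancreatic cell function". Data management and analysis uses it in two ways. OGTT outcomes are among the measures whose change "between pre and post exercise intervention will be tested using the paired t-test", with linear regression of the changes on alcohol use as a further analysis. The same section also says: "For categorical variables (e.g., glucose at 2 h, HOMA-IR, HOMA-b) clinical cutoff values will also be used". It does not state the cutoff values.

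**The concern.** HOMA is a named index with fixed constants. Two of the three constants in the sentence are the mg/dL versions and the third is not. The printed 60 is also not a leftover mmol/L value, because that would be 20.

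Whole-body glucose-insulin dynamics are part of the primary outcome in the Abstract. HOMA-β is not named there, but it is one of the OGTT measures that describe those dynamics. An analyst who codes the formula as printed would report HOMA-β on a scale that no other study uses. Setting such values against a clinical cutoff from the standard scale would push participants below it. If nearly everyone falls below it both before and after exercise, the categorical comparison has little room to show change.

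**Working it through.** **Inputs from the article.** HOMA-IR divisor 405; HOMA-β offset 63; HOMA-β multiplier 60; glucose in mg/dL and insulin in µU/mL (all from the OGTT subsection). Eligible fasting glucose: "Fasting plasma glucose between 94 and 124 mg/dl" (Table 1; the Abstract and the Screening section differ by 1 mg/dL at one end, which is immaterial here).

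**Inputs not in the article.** The standard mmol/L forms, HOMA-IR = G × I / 22.5 and HOMA-β = 20 × I / (G − 3.5), and the conversion of 18 mg/dL per mmol/L.

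**Step 1: convert each constant.**
- HOMA-IR divisor: 22.5 × 18 = 405, as printed.
- HOMA-β offset: 3.5 × 18 = 63, as printed.
- HOMA-β multiplier: 20 × 18 = 360; printed 60. The ratio is 360 / 60 = 6.
- Reverse check: 60 / 18 = 3.33, which is not a HOMA constant.

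**Step 2: check the two formulas against each other.** At insulin 5 µU/mL, HOMA-IR equals 1 when glucose is 405 / 5 = 81 mg/dL. On the standard scale this point corresponds to 100% β-cell function. With 360: 360 × 5 / (81 − 63) = 100. With 60: 60 × 5 / (81 − 63) = 16.7.

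**Step 3: size within the eligible range.** The article gives no insulin values, so 10 and 20 µU/mL are assumed.

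| Glucose (mg/dL) | Insulin (µU/mL) | Multiplier 60 | Multiplier 360 |
|---|---|---|---|
| 94 | 10 | 19.4 | 116.1 |
| 110 | 10 | 12.8 | 76.6 |
| 124 | 10 | 9.8 | 59.0 |
| 94 | 20 | 38.7 | 232.3 |
| 110 | 20 | 25.5 | 153.2 |
| 124 | 20 | 19.7 | 118.0 |

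The insulin needed for a HOMA-β of 100 is 100 × (G − 63) / multiplier. At 94, 110 and 124 mg/dL this is 51.7, 78.3 and 101.7 µU/mL with 60, against 8.6, 13.1 and 16.9 with 360.

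**Step 4: effect on a cutoff.** Let T be the true value and c a cutoff on the standard scale. The printed formula returns T / 6, which is below c whenever T < 6c. Participants with T from c up to 6c are therefore wrongly placed below. Those with T < c, or T of at least 6c, are placed correctly.

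The share affected depends on c and on the insulin distribution. As an illustration only, assume glucose uniform on 94 to 124 mg/dL and insulin log-normal with median 12 µU/mL and log-SD 0.6:

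| Assumed cutoff | Below it, multiplier 60 | Below it, multiplier 360 | Misclassified |
|---|---|---|---|
| 50 | 96.5% | 15.2% | 81% |
| 80 | 99.5% | 38.9% | 61% |
| 100 | 99.8% | 52.9% | 47% |
| 150 | 100% | 76.4% | 24% |

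**Step 5: effect on the tests.** A constant factor multiplies each paired difference and its standard error alike, so t and p do not change. The same holds for a regression with the change as dependent variable: coefficients and standard errors shrink together. One simulated data set of 33 pairs gave t = −1.40 and p = 0.171 with either multiplier. Percent changes are also unaffected, because the factor cancels.

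**The case against.** The strongest reply is that this is an error of print and not of data. The OGTT subsection is a short summary that refers to an earlier publication for its methods. Neither that publication nor the analysis code is shown, and a lost leading 3 would turn 360 into 60. The Results section adds some support: Phase 1, citing the same publication, found higher odds of decreased HOMA-β with at-risk alcohol use. An odds result needs participants on both sides of the split, which would be hard to obtain if nearly everyone lay below it. This leaves a misprint open but does not settle it, because the Phase 1 split is not given and could have been set on the same scale as the values.

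It can also be said that the main inference is safe. HOMA-β is one derived index among many; HOMA-IR, glucose, insulin, C-peptide, fitness and bioenergetic outcomes do not use the multiplier. The cutoffs are an additional analysis, and HOMA-β can be recomputed from fasting glucose and insulin. All of this stands and limits the damage. It does not make the printed formula right.

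A reader might infer that every HOMA-β value in the trial is six times too low, that any cutoff misclassifies, or that the share below a cutoff is also out by a factor of six. The documents support none of these. The first needs the code to follow the text. The second fails for a cutoff derived from the same values, such as a sample median. The third is wrong in principle: in the illustration the ratio of the shares is about 6.3 at a cutoff of 50 (96.5 / 15.2), 1.9 at 100 (99.8 / 52.9) and 1.3 at 150 (100 / 76.4).

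**Conclusion.** The formula is wrong as printed. In the stated units the multiplier consistent with 405 and 63 is 360, and the printed formula gives exactly one-sixth of HOMA-β. This rests on the standard HOMA definition, which the two other constants in the sentence confirm.

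The consequences are conditional. If 60 is what the code uses, reported HOMA-β levels, mean changes and regression coefficients are too small by a factor of six, and a clinical cutoff on the standard scale misplaces everyone whose true value lies between it and six times it. No hypothesis test on continuous HOMA-β changes. The number misclassified is unknown; the percentages above illustrate assumed inputs and do not estimate what happens in this trial.

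**What to change.** In the OGTT subsection, replace 60 with 360, so that HOMA-β (%) = 360 × fasting insulin (µU/mL) / (fasting glucose (mg/dL) − 63). Check which constant the analysis code uses. Only if it is 60, recompute the pre- and post-intervention HOMA-β values and their classification before the Phase 2 analysis. State the HOMA-β cutoff and apply it on the same scale as the values.

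The cost is one number in the text and one check of the code, plus a recalculation from fasting glucose and insulin if needed. No new data are required.
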